### Outcomes

The outcomes will be collected at each follow-up time point (1st, 3rd, 6th, 12th, 18th, and 24th months).

#### Primary outcomes

While thrombotic events are a critical consequence of AF, the incidence rate of these events in patients who are adequately anticoagulated is generally lower than the incidence of bleeding events. Consequently, the study’s primary outcomes comprise any bleeding events, both major and minor. Major bleeding events [32] include fatal hemorrhage, life-threatening bleeding, and severe bleeding requiring treatment or assessment. Severe bleeding can manifest as gastric intestinal hemorrhage, joint hematoma, retroperitoneal hemorrhage, fundus hemorrhage, urine, hemoptysis, or require blood transfusion of at least two units. In contrast, minor bleeding events, such as mild nasal hemorrhage, endoscopic hematuria, skin stasis, or mild hemorrhoids, do not lead to serious consequences [33].

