### Randomization and blinding

To avoid any risk of contamination between the SDM and control groups, cluster randomization will be implemented in this trial. The intervention provided to patients with AF will be grouped by clinicians in a single community health service center. Computer-generated randomization will be used to allocate the intervention and control groups in a 1:1 ratio following AF confirmation. The allocation results of each community health center will be told to the administrators by telephone. Each administrator only knows the result of his or her own site. The researchers, participants, and data analysts will not be blinded, but the participants will not be allowed to know the outcomes of this study.

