### Interventions

#### Introduction

Community health service centers that are randomized to the SDM group will utilize the SDM tool to manage AF patients. The medical specialists involved in this study will have access to the SDM tool. The anticoagulation regimens for AF patients will be determined through communication between the clinicians and patients based on the suggestions and information provided by the SDM tool. This includes anticoagulation strategies that have a corresponding net clinical benefit (NCB), cost of each anticoagulant, blood examination of warfarin, and other relevant considerations. Clinicians will prescribe dosage regimens and order appropriate laboratory monitoring based on the recommendations of the SDM tool. Furthermore, this SDM tool can also assist clinicians with anticoagulation regimes in AF patients with specific circumstances, such as adjuvant bridging therapy, periprocedural anticoagulation recommendations, and drug regimen adjustments for end-organ function, weight, and concomitant interactions. With the help of the SDM tool, pharmacists can provide comprehensive patient education, including indications for the therapy, medication intake, medication interactions, laboratory monitoring, activity, diet, side effects, pregnancy, procedures, safety precautions, and self-care. The SDM tool will also enable the tracking of bleeding and other adverse events relevant to anticoagulation, as well as assessing patients’ knowledge, adherence, and satisfaction with anticoagulation therapy. The tool will automatically schedule the follow-up scheme, and the anticoagulation therapy will be reassessed based on the follow-up data of the patients. The records and information of the patients will be obtained from the SDM tool cloud platform. In contrast, the control group will receive the usual care based on the clinicians’ usual approach.

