#### Secondary outcomes

The study’s secondary outcomes include the accordance of stroke prophylaxis for AF according to the current guidelines, the percentage of time in the target INR range for patients using warfarin, the occurrences of major bleeding and thrombosis events, and the OAC knowledge, adherence, and satisfaction of AF patients receiving anticoagulation therapy. The study will evaluate stroke prophylaxis for AF using a flow chart (Fig. 2) and guidelines for dabigatran, rivaroxaban, and edoxaban (Table 2). The anticoagulation quality of warfarin will be assessed using the TTR, and the therapeutic range of INR for patients with AF is set between 1.8 and 3.0 [34]. The study considers TTR levels of 65% or higher as good anticoagulation quality. Thrombosis events, including ischemic stroke, systemic embolism, and transient ischemic attacks, will be confirmed by imaging methods such as ultrasound, CT, or MRI. To evaluate patients’ knowledge, adherence, and satisfaction with anticoagulation therapy, the study will use AKT, MARS-5, and ACTS. The AKT comprises 28 items assessing the general anticoagulation knowledge for all available OAC and a specific section for VKA therapy. The MARS-5 assesses common patterns of nonadherent behavior, and the ACTS evaluates the burdens and benefits of anticoagulation treatment and its overall impact (see Additional file 2).

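### The line between major and minor bleeding rests partly on a bleed needing assessment and on ungraded, overlapping site lists, which leaves the secondary major-bleeding outcome open to care contact and site judgement

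*Protocol article*

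**What the plan says.** The Primary outcomes section sets the endpoint as any bleeding: "the study’s primary outcomes comprise any bleeding events, both major and minor". It then gives a rule for each class.

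- **Major:** "Major bleeding events [32] include fatal hemorrhage, life-threatening bleeding, and severe bleeding requiring treatment or assessment". The next sentence explains how the severe category can show itself. After gastrointestinal bleeding it lists "joint hematoma, retroperitoneal hemorrhage, fundus hemorrhage, urine, hemoptysis, or require blood transfusion of at least two units".
- **Minor:** "minor bleeding events, such as mild nasal hemorrhage, endoscopic hematuria, skin stasis, or mild hemorrhoids, do not lead to serious consequences".

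Major bleeding on its own is a secondary outcome: the Secondary outcomes section lists "the occurrences of major bleeding and thrombosis events".

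Three further statements bear on how events come to be classified:

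- Randomization and blinding: "The researchers, participants, and data analysts will not be blinded".
- Interventions, Introduction: "The SDM tool will also enable the tracking of bleeding and other adverse events relevant to anticoagulation".
- Follow-up: control patients who cannot come to a scheduled visit may be followed by telephone. The section makes no such statement for the SDM arm.

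**The concern.** A severity class should depend on the bleed. Part of this rule depends on what is done about the bleed. Treatment says something about severity, but a need for assessment says little: most bleeds that an anticoagulated patient reports to a clinician will be thought to need some evaluation. The word that should carry the distinction, *severe*, is explained by sites with no volume, haemoglobin, intervention or admission criterion. The only measurable item, two units transfused, is an alternative and not a requirement.

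Two kinds of event fit both sides of the line, so the class is left to whoever records it, and that person knows the arm. If bleeds come to clinical attention differently in the two arms, the share labelled major can differ at equal severity.

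At stake is the reading of one secondary outcome. It is not a trivial one: the tool steers the choice of anticoagulant, and the protocol provides no data monitoring committee.

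**Working it through.** **1. Does the plan's own calculation depend on the split?** The Sample size section gives 20% bleeding, a reduction of 15 (read as percentage points, so 5%), 80% power, two-sided 5%, 20% loss and a design effect of 2.

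- Uncorrected: n = [1.960·√(2·0.125·0.875) + 0.842·√(0.16 + 0.0475)]² / 0.15² ≈ 75.1, so 76 per group.
- With continuity correction: (75.1/4)·[1 + √(1 + 4/(75.1·0.15))]² ≈ 88 per group, as stated.
- Loss: 88/0.80 = 110. Total: 110 × 2 groups × 2 = 440, as stated.

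The figures reproduce. They are for any bleeding, so moving an event between major and minor changes neither the sample size nor the primary outcome.

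**2. The two definitions side by side.**

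| Event | Major side | Minor side | Separated by a stated criterion? |
|---|---|---|---|
| Fatal or life-threatening | Named | – | Yes, by severity |
| Two or more units transfused | Named | – | Yes, measurable |
| Urinary bleeding | Listed as *urine*, no grade | Listed as endoscopic haematuria | No |
| Haemorrhoidal bleed | Can be read as gastrointestinal | Listed if *mild* | Only by *mild*, undefined |
| Haemoptysis | Listed, no grade | Not listed | Only by *severe*, undefined |
| Gastrointestinal bleed without transfusion | Listed, no grade | Not listed | Only by *severe*, undefined |

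The first two rows work. In the other four the recorder must decide whether the bleed is severe, and the only further condition in the sentence is that it requires treatment or assessment.

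**3. Can classification differ by arm?** Three features make it possible: unblinded staff, bleeding tracked through the tool in one arm, and telephone contact stated for the other arm only. A bleed reported by telephone is less likely to be examined. Against this, both arms have the same six visits (months 1, 3, 6, 12, 18 and 24) and the same questionnaires. The last two features would tend to raise the major count in the SDM arm. Unblinded judgement could push either way.

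**4. Illustration on assumed values.** Assume 220 per arm (440/2) and 20% with any bleed in both arms, that is 44 patients each. Let only the share labelled major differ. These shares are not in the documents. The last two columns give the approximate chance that the false difference is nominally significant in that direction (two-sided 5% test).

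| Share major, control vs SDM | Major bleeding | Patients | Ratio | Clustering ignored | Design effect 2 (110 effective per arm) |
|---|---|---|---|---|---|
| equal | equal | equal | 1.0 | no bias | no bias |
| 20% vs 30% | 4% vs 6% | 8.8 vs 13.2 | 1.5 | 16% | 10% |
| 20% vs 40% | 4% vs 8% | 8.8 vs 17.6 | 2.0 | 42% | 24% |
| 30% vs 50% | 6% vs 10% | 13.2 vs 22.0 | 1.67 | 34% | 19% |

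With 176 per arm (220 × 0.80, the planned loss) the chances are 14%, 35% and 28%, or 9%, 20% and 16% with design effect 2. The any-bleeding comparison is 20% vs 20% in every row.

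**The case against.** A reader might infer that any bleed a doctor looks at becomes major, so that the outcome measures care-seeking and not severity. The text does not support that. *Severe* remains a necessary condition. The bleed must require assessment, which is not the same as receiving it. The sites are examples of how severe bleeding may appear and are not sufficient on their own. The fatal, life-threatening and two-unit limbs are severity criteria, and minor bleeds are bounded by having no serious consequences.

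Other points on that side:

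- The overlap is limited. Two minor items are qualified as mild, and the two urinary terms may be wording slips.
- Both definitions cite sources, and the article rests on a full protocol (version 3.0). Neither is shown, and either may be finer.
- The schedule of visits is common to both arms. The tool is said to enable tracking of bleeding, not to create extra assessments. Lack of blinding and telephone follow-up are general ascertainment issues.

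Most of this stands, and it limits the point to susceptibility. It does not remove it. The article states a rule instead of leaving one to a fuller document, and that rule uses an ungraded *severe* together with a contact-based condition. If the urinary terms are slips, they still need correcting wherever events are classified from this wording. If the cited source or full protocol is finer, the article departs from it and the two should be reconciled.

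**Conclusion.** The definition should be tightened. As worded, the secondary major-bleeding outcome is open to influence from care contact and from unblinded site judgement, mainly for urinary, gastrointestinal or haemorrhoidal bleeds and haemoptysis. No bias has been shown, and its size cannot be derived from the documents. The ratios of 1.5 to 2.0 rest wholly on assumed labelling shares and would be 1.0 if both arms label alike.

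It would also be wrong to infer that the main result is at risk. The primary outcome counts major and minor bleeds together, and 88, 110 and 440 do not depend on the split.

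**What to change.** Reword the definition and derive the class by rule:

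1. Remove assessment as a criterion for major bleeding.
2. Keep the fatal, life-threatening and at-least-two-unit limbs.
3. Count any other bleed as major only if it is symptomatic in a named critical site (for example retroperitoneal, intra-articular, intraocular or intracranial) or meets a pre-stated objective criterion, such as a fixed haemoglobin fall where measured, or hospital admission.
4. Make the urinary categories, and the gastrointestinal and haemorrhoidal categories, mutually exclusive. Bleeds that do not meet item 2 or 3 are minor.
5. Record site, units transfused, haemoglobin and admission for each bleed, and derive the class from these facts and not from the site's label. Apply the rule identically in both arms and to events already recorded.

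**Cost.** A wording change and a few event fields in the CRF and the tool. Fewer events will count as major. Haemoglobin is not listed in the schedule of study activities and will be missing for some events, perhaps more often where contact was by telephone. It and admission still depend on someone acting, so the rule reduces dependence on care contact without abolishing it. Enrolment began in October 2022, so the change comes mid-trial and must be dated and documented before the outcome data are analysed. The primary outcome and sample size stay as they are.

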#### Secondary outcomes

The study’s secondary outcomes include the accordance of stroke prophylaxis for AF according to the current guidelines, the percentage of time in the target INR range for patients using warfarin, the occurrences of major bleeding and thrombosis events, and the OAC knowledge, adherence, and satisfaction of AF patients receiving anticoagulation therapy. The study will evaluate stroke prophylaxis for AF using a flow chart (Fig. 2) and guidelines for dabigatran, rivaroxaban, and edoxaban (Table 2). The anticoagulation quality of warfarin will be assessed using the TTR, and the therapeutic range of INR for patients with AF is set between 1.8 and 3.0 [34]. The study considers TTR levels of 65% or higher as good anticoagulation quality. Thrombosis events, including ischemic stroke, systemic embolism, and transient ischemic attacks, will be confirmed by imaging methods such as ultrasound, CT, or MRI. To evaluate patients’ knowledge, adherence, and satisfaction with anticoagulation therapy, the study will use AKT, MARS-5, and ACTS. The AKT comprises 28 items assessing the general anticoagulation knowledge for all available OAC and a specific section for VKA therapy. The MARS-5 assesses common patterns of nonadherent behavior, and the ACTS evaluates the burdens and benefits of anticoagulation treatment and its overall impact (see Additional file 2).

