### Follow-up

In this study, each patient enrolled will be monitored for at least 2 years, regardless of whether they meet the study’s endpoint or not. For both the SDM group and the control group, the same set of questionnaires will be used for consistency in recording follow-up data. The enrolled patients will undergo follow-ups on the 1st, 3rd, 6th, 12th, 18th, and 24th months through outpatient clinic visits. The follow-up plan will be automatically arranged using the SDM tool. Patient anticoagulation therapy will be re-evaluated based on follow-up data, and information on patients’ records and past data will be retrieved from the SDM tool’s cloud platform. At each follow-up time point, patients in the SDM group will complete the questionnaires within the tool, while patients in the control group will complete the questionnaires within the clinical case report form (CRF). A designated medical staff member will send text reminders to patients to attend follow-ups. Patients in the control group who cannot attend scheduled follow-ups at the community health service centers can be followed up by telephone.

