### Sample size

This multicenter, cluster-randomized clinical trial aims to evaluate the occurrence of bleeding events as the primary outcome. The anticoagulation bleeding rate of patients with AF in our hospital was previously found to be 20% [24], and an effective intervention reduces the incidence of bleeding by 15% [35]. We set the power at 80% with a bilateral two-tailed significance of 5%. To achieve a sample size of 88 cases in both the intervention and control groups, with a 20% loss to follow-up rate, we estimated a minimum of 110 cases in each group. However, taking the clustering into account, we increased the sample size to account for the design effect to achieve the required statistical power under cluster randomization. Therefore, using the bleeding rate as the calculating target and a design effect of 2, we estimated a sample size of 440, which was calculated using the PASS software version 15.

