### Strengths and limitations

This study has significant advantages, as it is a large-scale multicenter cluster randomized controlled trial involving a substantial number of participants. However, there are some limitations to this research. Firstly, the 24-month period may not be long enough to assess the effect on clinical outcomes such as thromboembolic events. Therefore, future studies should consider longer follow-up periods to evaluate the effects of the intervention over an extended period. Secondly, it is possible that those who agreed to participate in the research might be more interested in their own health, leading to a higher adherence to medication therapy than the general population with AF. This could potentially affect the generalizability of the study findings.

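### The thrombosis outcome requires imaging confirmation for transient ischemic attack, an event that imaging typically cannot confirm

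*Protocol article*

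**What the plan says.** The Secondary outcomes section lists "the occurrences of major bleeding and thrombosis events" among the secondary outcomes. It then gives a single confirmation rule: "Thrombosis events, including ischemic stroke, systemic embolism, and transient ischemic attacks, will be confirmed by imaging methods such as ultrasound, CT, or MRI". The rule names TIA. Nothing else in the article gives TIA a separate criterion or says what an image would have to show for a TIA to be confirmed.

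Other statements bear on how the rule would operate:

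- Table 3 (Schedule of study activities) lists no brain or vascular imaging at baseline or at any of the six visits. The nearest item is ejection fraction, a measure of heart function. A scan for a suspected event therefore happens only if someone orders it.
- Randomization and blinding: "The researchers, participants, and data analysts will not be blinded".
- Interventions, on the SDM (shared decision-making) arm: "The SDM tool will also enable the tracking of bleeding and other adverse events relevant to anticoagulation".
- Follow-up: "Patients in the control group who cannot attend scheduled follow-ups at the community health service centers can be followed up by telephone". The SDM arm has no matching provision.
- Strengths and limitations accepts that "the 24-month period may not be long enough to assess the effect on clinical outcomes such as thromboembolic events".

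**The concern.** One rule covers three events that are established in different ways. Ischemic stroke and systemic embolism normally leave something to see. A TIA is a focal deficit that resolves, and imaging is typically done to show that no infarct or hemorrhage is present. A negative scan supports the diagnosis of TIA, whereas a rule that demands imaging confirmation seems to count it against the diagnosis.

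The primary outcome is any bleeding, and bleeding can fall because patients receive less anticoagulation. Thrombosis is the clinical-event outcome that would show the price of such a change. The Primary outcomes section already expects thrombotic events to be fewer than bleeding events in adequately anticoagulated patients. With so sparse an outcome, what counts as an event needs to be unambiguous and the same in both arms.

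**Working it through.** **1. The plan's own figure.** The only sample size calculation is for bleeding. Its inputs (Sample size) are a 20% control rate, a reduction of 15 (which reproduces as percentage points, 20% to 5%), 80% power and two-sided 5%.

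- n = [1.960·√(2·0.125·0.875) + 0.842·√(0.20·0.80 + 0.05·0.95)]² / 0.15², which gives 76 per arm.
- With the continuity correction this becomes 88 per arm.
- 88 / (1 − 0.20) = 110, and 110 × 2 arms × design effect 2 = 440.

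The stated figures reproduce. No thrombosis rate enters them, so a change to the TIA rule leaves them as they are.

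**2. What the rule means for a TIA.** The wording allows two readings.

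- *Strict: imaging must show the event.* A typical TIA, with a negative scan, is not confirmed and does not count. An event with an acute lesion would generally be classed as ischemic stroke, so it still counts in the total, but as stroke. The TIA component is then close to empty.
- *Loose: an imaging work-up must have been done.* A TIA with a negative scan counts, but the same TIA without a scan does not. Because imaging is unscheduled, counting depends on who is referred.

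Neither reading gives a usable TIA criterion.

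**3. Could counting differ by arm?** Staff and patients know the allocation, event tracking through the tool is described for the SDM arm, and telephone follow-up is named only for control patients. A telephone contact does not itself produce a scan. These features permit a difference in scanning. They do not show one.

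**4. Illustration only.** The article gives none of the quantities needed, so every input here is assumed. Let s be the TIA share of true thrombosis events and q the share of TIAs with positive imaging. All strokes and emboli are taken as confirmed.

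Share of events kept under the strict reading, with every TIA scanned: 1 − s + s·q.

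| s | q = 0 | q = 0.5 |
|---|---|---|
| 0.2 | 0.80 | 0.90 |
| 0.3 | 0.70 | 0.85 |
| 0.5 | 0.50 | 0.75 |

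Now suppose there is no true effect and TIAs are scanned with probability a in one arm and b in the other. The apparent ratio of event counts is (1 − s + s·q·a) / (1 − s + s·q·b). Take a 30-point gap (90% vs 60%, or 80% vs 50%) and s from 0.2 to 0.5.

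- Strict reading, q from 0.3 to 0.5: from 0.854/0.836 = 1.02 to 0.700/0.625 = 1.12.
- Loose reading, where any scan suffices (q = 1): from 0.98/0.92 = 1.07 to 0.90/0.75 = 1.20.

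The less-scanned arm looks better in each case. The spread shows how little can be said about size without data.

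**The case against.** The best defense is that one sentence in a condensed article summarizes three event types. It may mean only that suspected events get an imaging work-up, which for TIA would exclude infarct and hemorrhage, and detailed event criteria may sit in the full protocol or case report form. Part of this stands: the text does not expressly demand a positive lesion, so the strict reading is not the only one. It does not remove the point, because the article states a criterion and applies it to TIA by name, and the loose reading has its own fault. If the full protocol already defines TIA separately, the sentence should be brought into line with it.

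It is also fair to say that imaging evidence is a sensible safeguard in an unblinded trial. That stands, and is a reason to keep the imaging rule for stroke and systemic embolism.

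A reader might infer four stronger things that the article does not support:

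- *That most TIAs, or a definite number of events, are lost.* If 4–6% of 440 patients had an event (17.6–26.4) and 15–25% of those were dropped, about 3–7 would go. On the 352 patients left after 20% loss (440 × 0.80), the same assumptions give 14–21 events and about 2–5 lost. All these rates are assumed.
- *That thrombosis is the only check on stroke protection.* Guideline accordance, time in therapeutic range and adherence are also secondary outcomes and also reflect it. Thrombosis is the only one of these that is a clinical event.
- *That scanning will differ by arm.* The design allows it, but no referral pattern or scan rate is given.
- *That unscanned strokes belong in the main count.* Classification of such events by unblinded staff would trade one weakness for another.

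**Conclusion.** The point holds as a badly fixed outcome rule. Imaging confirmation is stated for TIA, where it either excludes imaging-negative events or makes counting depend on unscheduled scans in an open-label trial. This rests on the article's wording and on the clinical nature of TIA, not on any assumed rate. The size of the effect cannot be given from the document, and the ranges in the working are illustrations. The consequence is confined to one component of one secondary outcome. It is worth correcting because the outcome is sparse and is the clinical counterweight to a bleeding endpoint.

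**What to change.** Replace the single rule with two.

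- **Main thrombosis outcome:** ischemic stroke plus systemic embolism, confirmed by imaging, reported together.
- **TIA, reported separately:** a documented sudden focal deficit with full resolution, and no acute infarct or hemorrhage on any imaging performed. The same rule applies in both arms.
- **Sensitivity analysis only:** strokes or deaths without imaging may be recorded as probable and added there.

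The cost is a wording change and two case report form fields: one for the clinical features of a suspected TIA, and one for whether imaging was done and what it showed. The sample size and the primary analysis do not change. The downside is that a clinically diagnosed TIA is softer when those recording it know the allocation. Keeping it out of the main thrombosis outcome contains that risk.
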